### Study setting and participant characteristics

The data collection, subject recruitment and gaming will be carried out in outpatient services (e.g., outpatient psychiatric units, day hospitals, residential care homes). Specific inclusion criteria mandate that patients should have a formal diagnosis of schizophrenia spectrum disorder (Diagnostic and Statistical Manual of Mental Disorders, fifth edition, DSM-5), and be between 18 and 60 years old. We will intentionally recruit people who are non-active, less-experienced gamers [19]. Participants will be required to be able to speak Cantonese, be able to participate based on their own free will and have the ability to provide written informed consent. Participants should have a cognitive status deemed suitable for study participation based on ‘the judgement standard’, i.e., be approved by the staff responsible of the treatment based on their clinical expertise.

The exclusion criteria are: 1) meeting the diagnostic criteria for a current major depressive, manic or hypomanic episode (DSM-5), or mental retardation, 2) having severe visual impairment, 3) being an active gamer (i.e. gaming > 5 h/week [17]), 4) displaying a lack of ability to decide one’s own participation, 5) substance abuse (other than nicotine dependence), 6) head injury, hemiplegia, or other neurological disorder, 7) electroconvulsive therapy (ECT) in the past six months, 8) having a lack of Magnetic Resonance Imaging (MRI) compatibility (e.g., cardiac pacemakers, metallic implants, restless behaviour, claustrophobia), and 9) pregnancy.

### Power analysis and sample size

We have calculated the sample size based on the primary outcome as follows: (1) the number of actual pairwise tests to be made for the efficacy of the primary outcome and (2) the two-level modelling approach in the final data analysis, in which the type I error has been adjusted. The statistical efficiency will be ensured using the multivariate analysis of variance (MANOVA) method for multiple group comparison. First, given that video gaming is a fairly novel strategy, we will base the sample size calculation (a priori) [32] on a cognitive-efficacy meta-analysis for patients with schizophrenia [33] showing an overall effect size (ES, Cohen’s *d*) of 0.58 on verbal working memory (a primary outcome). Based on our hypothesis, the primary endpoints will be the effects on verbal working memory after 3 and 6 months of cognitive training group (CogniFit), compared with the other two groups: cognitive training vs. entertainment gaming, cognitive training vs. non-gaming control group, and entertainment gaming vs. non-gaming control group. Four pairwise interactions between the contrast of the two comparisons and the two time points will be tested. For multiple comparison tests of four, for a type I error level of 5% (two-sided), an adjusted significant level should be α/2 = (1- (1–0.05)4) /2 = 0.01274 /2 = 0.0064, and the corresponding z score for a one-tailed test should be 2.49. Given the effect size 0.58, assuming equal sample size of the three groups, with a statistical power of 0.8 and α= 0.01274*,* we will require at least 198 subjects (66 per group at follow-up phase) by applying the equation, 2(Z1-β + Z1-α/2)2 / ES2. According to a meta-analysis [33], the total sample size in previous cognitive training studies was around 50 (range 10–138).

Using evidence-based rationale for patient flow in this study, we can assume that about 60% of patients screened will not be eligible for the study, due to age or lack of capacity to participate in the study [34]. Based on existing literature, we anticipate that about 45% of patients with schizophrenia will refuse to participate in the RCT studies [33], about 60% of patients screened will not be eligible for the study, and around 16% will drop out during the course of intervention [35]. Thus, we need a total of 1073 subjects to be approached and 237 participants to be randomly allocated to three study groups (79 patients/group) to ensure a final sample of 198 participants in the follow-ups (66 patients/group). These numbers are realistic given that the total number of patients with schizophrenia in our study sites is about 5500, and the total number of schizophrenia patients in Hong Kong is 40,000.

For the EEG analysis, a sub-sample of 50 patients in each group will be recruited (*N* = 150). For neuroimaging assessment using 3 T MRI and rs-fMRI, a sub-sample of 126 participants from our total sample (*N* = 198) will need (63%) to be randomised at baseline. Randomisation will be based on a list of computer-generated random numbers. We assume that 30% will drop-out between baseline and the 3-month follow-up assessment, which leaves us with 29 patients in each group (a total of 87 participants at baseline). The sample size will be appropriate for our neuroimaging assessment; the average number of participants in RCT studies assessing patient cognition [33] or changes in brain structure has been about 20 [14]. The flow-chart of the study is presented in Fig. 1.

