### The hypotheses

Primary hypothesis:
Cognitive training with computerised exercises is more effective than entertainment video gaming or the non-gaming control in improving patients’ working memory at a 3-month and/or 6-month follow-up.

Secondary hypotheses:
2.Cognitive training with computerised exercises is more effective than entertainment video gaming and the non-gaming control in improving patients’ cognitive and social functioning, experience of pleasure, and self-efficacy at a 3-month and/or 6-month follow-up.3.Cognitive training with computerised exercises is more effective than entertainment video gaming and the non-gaming control in improving negative symptoms in schizophrenia at a 3-month and/or 6-month follow-up.4.Cognitive training with computerised exercises is more effective than entertainment video gaming and the non-gaming control in improving neurocognitive outcomes (EEG signals, brain activity and structure) at a 3-month follow-up.

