In the main analysis, we will estimate and test efficacy of interventions on the primary and secondary outcomes. Based on the intention-to-treat principle, we will first assess intervention effects on the primary outcome, verbal working memory, by means of multilevel modelling analysis. A two-level model can be built with repeated time points at level 1, and patients at level 2. Two indicator variables, G2 and G3, will be included in the fixed part of the model to estimate and test mean differences between the cognitive training group with computerised exercises (G1) and the entertainment gaming group (G2), as well as between G1 and the non-gaming control group (G3). The baseline difference between G2 and G3 can be tested using a Ward test, based on the regression coefficient estimates of the two indicators. For changes in the outcome over time, two more indicators, variables T2 and T3, in contrast to the baseline time point, T1, will be included in the fixed part of the model to estimate changes from baseline to 3 months, and from baseline to 6 months. To assess the effects of interventions over time, interaction terms between the treatment group indicators, G2 and G3, and time indicators, T2 and T3, will be included in the fixed part of the model. The significantly different demographics between groups identified in the first step of the analysis and other possible confounders will be adjusted by including them in the main effect model. The within-patient random effects of the outcome measurements will naturally be taken into account by the level two variance in the model. A pairwise comparison and other hypotheses on the intervention effects can be tested using a generalised Ward test with an adequate degree of freedom from the modelling analysis. This analysis approach has two main advantages: a statistically highly efficiency and taking missing data into account. The effects of interventions on other secondary outcome measures, normally distributed and measured at three time points, such as patients’ cognitive and social functioning, experience of pleasure, and self-efficacy, will be analysed using the same model, but a separate model for each outcome. A multilevel logistic model will be used for outcomes in binary form, and multilevel multinomial models will be used for ordinal or nominal outcomes. For outcomes measured at two time points only, such as neurocognitive outcomes, the model will have only one time indicator with two interaction terms to test the efficacy of cognitive training with computerised exercises three months into the trial.

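### The primary endpoints list three pairwise contrasts at two times, but the adjusted alpha and the sample size cover only the two contrasts with cognitive training

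*Protocol article*

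**What the plan says.** Under Power analysis and sample size, the protocol bases the sample size on the number of pairwise tests to be made on the primary outcome. It introduces the primary endpoints as effects on verbal working memory at 3 and 6 months in the cognitive training group against the other two groups. It then lists three contrasts: "cognitive training vs. entertainment gaming, cognitive training vs. non-gaming control group, and entertainment gaming vs. non-gaming control group". The sentence that follows reads "Four pairwise interactions between the contrast of the two comparisons and the two time points will be tested", and the adjustment is set accordingly: "For multiple comparison tests of four, for a type I error level of 5% (two-sided". The per-test level is given as 0.01274, "the corresponding z score for a one-tailed test should be 2.49", and 66 per group follow for an effect size of 0.58 "with a statistical power of 0.8".

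Elsewhere:

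- The primary hypothesis (The hypotheses) says that cognitive training is "more effective than entertainment video gaming or the non-gaming control". That is two comparisons.
- Trial design gives the reason for three arms as testing the superiority of cognitive training over each of the two controls.
- The analysis model (Cognitive and clinical outcomes) takes cognitive training as the reference group, and "interaction terms between the treatment group indicators, G2 and G3, and time indicators, T2 and T3, will be included". That is four terms. The same section adds "A pairwise comparison and other hypotheses on the intervention effects can be tested".
- The end of that section treats P < 0.05 as significant in all tests.

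**The concern.** Two adjacent sentences define the primary family differently. Read literally, the first puts entertainment gaming versus non-gaming control among the primary endpoints, while the second leaves it out of the error control. The model section allows further pairwise contrasts without giving them a status. An analyst could therefore report the entertainment game against control as a primary result with no multiplicity allowance, and cite the protocol for it. An analyst who kept to four tests could cite the protocol equally well.

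What is at stake is whether the 5% family-wise error and the 80% power describe the family that will actually be tested.

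**Working it through.** **Inputs from the protocol.** Family-wise alpha 5% two-sided; effect size 0.58; power 0.80; equal groups; 66 per group at follow-up; dropout 16%. **Assumed:** the correlation between 3- and 6-month results, which the protocol does not give, varied from 0.3 to 0.9.

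**1. The protocol's own figure, four tests.**
- Sidak level: 1 − 0.95^(1/4) = 0.01274, or 0.0064 per tail, z = 2.491. (The exponent prints as 4 in the text at hand. The printed result shows that 1/4 was meant, so this is not counted as an error.)
- n per group = 2(z + 0.8416)²/0.58² = 2 × (3.3325)²/0.3364 = 66.03. With z rounded to 2.49 it is 65.99.
- Power at 66 = Φ(0.58 × √33 − 2.491) = Φ(3.332 − 2.491) = Φ(0.841) = 80.0%.
- Family-wise error over four independent tests: 1 − (1 − 0.01274)^4 = 5.0%. With shared arms and correlation 0.3 to 0.7 it is about 4.7% to 4.2% by simulation.

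The protocol's figures reproduce.

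**2. Count of tests from the list.** 3 contrasts × 2 times = 6. Count from the next sentence: 2 × 2 = 4.

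**3. Six tests, each at 0.01274.** Simulated under the null, with each arm shared between contrasts:

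| Assumed 3–6 month correlation | Family-wise error |
|---|---|
| 0.3 | 6.6% |
| 0.5 | 6.3% |
| 0.7 | 5.9% |
| 0.9 | 5.0% |

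Under independence the figure would be 1 − (1 − 0.01274)^6 = 7.4%. Independence is impossible here: at each time the third contrast is the difference of the other two.

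**4. Six tests, properly controlled by Sidak.**
- Level: 1 − 0.95^(1/6) = 0.0085, z = 2.631.
- n per group = 2 × (2.631 + 0.8416)²/0.3364 = 71.7, so 72 per group, or 216 evaluable against 198. After 16% dropout, 72/0.84 = 85.7, so 86 per group, or 258 randomised against the 237 in the sample size section.
- Power at 66 = Φ(3.332 − 2.631) = Φ(0.701) = 75.8%. With the t distribution it is 74.4%.

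**5. The level in the analysis section.** Four tests at 0.05 give 1 − 0.95^4 = 18.5% if independent. With shared arms and correlation from 0 to 0.7, simulation gives about 17% to 15%.

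**The case against.** The strongest answer is that the protocol does settle the number of tests. The three-item list is introduced as cognitive training against the other two groups, in line with the hypothesis. The very next sentence fixes four tests on two comparisons. The primary hypothesis, the reason given for three arms and the four interaction terms in the model all agree, and only one clause points to six. The provision for other pairwise contrasts does not call them primary. On this view the arithmetic is right and one clause is loosely worded.

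Most of this stands: four tests is the likelier intent, and on that family the stated figures are correct. A reader might infer from the list that the trial has a six-test family and therefore fails its own 5% and 80%. The documents do not support that flat conclusion. A reader might also quote 7.4% as the error rate, but that figure needs an independence that shared arms rule out.

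The objection does not remove the contradiction. Both sentences are complete, current prose, and nowhere is the third contrast labelled secondary or exploratory. Nor is this a detail that an analysis plan would merely fill in, because the protocol itself states the endpoints, the test count and the level, and they disagree.

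**Conclusion.** The inconsistency is real, and its consequence is conditional and modest. With four primary tests, 0.01274 and 66 per group deliver the stated 5% and 80%. If entertainment gaming versus control is also confirmatory, one of the two gives way. Either the family-wise error is about 5.9% to 6.6% at assumed correlations of 0.7 to 0.3, with no inflation at 0.9, or power at 66 per group is about 75% at the six-test level. The power figure rests on the protocol's effect size of 0.58 and on its simple two-group formula. Sidak for six ignores the correlation between tests and is conservative here, so a method that used the correlation would lose less.

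Settling the family secures the 5% only if the adjusted level is carried into the analysis section. As written, the general P < 0.05 rule would undo the adjustment, and by more than the third contrast does.

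**What to change.** Remove entertainment gaming versus non-gaming control from the list of primary endpoints and name it a secondary contrast. Under Cognitive and clinical outcomes, state that the four primary tests (cognitive training against each control, at 3 and at 6 months) are judged at 0.01274, and limit P < 0.05 to the other tests. The 66 per group then stands unchanged.

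If the third contrast is to stay primary, use 0.0085 for each of the six tests and restate power at 66 per group as about 75%.

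The cost of the first option is one sentence in each of two sections and no extra participants. The downside is that entertainment gaming versus control becomes a secondary claim. Recruitment is reported as ongoing, so the family can still be fixed in advance of the results.

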### Trial design

The effectiveness of the intervention will be assessed using a controlled clinical trial with a pragmatic, three-arm parallel-group design. The three-arm design is chosen to explicitly test the superiority of the experimental cognitive training with computerised exercises (CogniFit) compared to the active control (entertainment games) and treatment as usual (non-gaming passive control) [31]. Since the objective of the study is to test the efficacy of the type of gaming (cognitive training with computerised exercises vs. entertainment gaming), having a three-arm trial is necessary to assess the effects of the gaming types separately.

To assess fidelity, we will use gaming diaries to verify whether the interventions have been delivered as intended (intervention fidelity) and confirm patient gaming activity (gaming frequency [number of gaming sessions per week], the length of each session [minutes], number of drop-outs). We will also analyse any information on the perceived strengths and limitations of interventions written in the patients’ diaries.

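### The 80% power is for one contrast, not for beating both controls at a visit (about 69%), and the adjusted level behind it never reaches the analysis text; Holm-Sidak on the four primary tests would be a cheap improvement

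*Protocol article*

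**What the plan says.** The protocol article, under Power analysis and sample size, counts the primary tests: "Four pairwise interactions between the contrast of the two comparisons and the two time points will be tested". It then fixes one level for all of them. "For multiple comparison tests of four, for a type I error level of 5% (two-sided), an adjusted significant level should be" 0.01274, which is halved to "0.0064, and the corresponding z score for a one-tailed test should be 2.49". The size follows from a two-group formula: "Given the effect size 0.58, assuming equal sample size of the three groups", "with a statistical power of 0.8 and" that adjusted alpha, "we will require at least 198 subjects (66 per group at follow-up phase"). The section also says that the type I error has been adjusted in the two-level model used for the final analysis.

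Two other sections bear on what must be shown. Trial design says that three arms were chosen to "test the superiority of the experimental cognitive training with computerised exercises (CogniFit) compared to the active control (entertainment games) and treatment as usual". The primary hypothesis, under The hypotheses, is looser: it joins the two controls by *or* and the two visits by *and/or*.

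The analysis text (Data analysis, Cognitive and clinical outcomes) says: "A pairwise comparison and other hypotheses on the intervention effects can be tested using a generalised Ward test". It gives no level there. The same subsection ends by applying a 95% confidence level and P < 0.05 to all tests.

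**The concern.** There are three linked points.

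- **What the 80% refers to.** A two-group formula at a per-test level gives the power of one contrast. A claim that needs two rejections has lower power, and the protocol gives no figure for it.
- **The rule is more conservative than it needs to be.** A single Sidak level is not relaxed after a rejection. A step-down version has the same first threshold and the same overall 5%, and it rejects everything that the single level rejects, and sometimes more.
- **The level does not reach the analysis.** If the closing sentence on P < 0.05 is followed literally, the four primary tests have no multiplicity control, although the sample size paid for it.

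At stake are the clarity of the primary claim, its type I error, and power that is available at no cost.

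**Working it through.** **Inputs from the protocol:** four tests; overall two-sided alpha 0.05; d = 0.58 for every comparison; power 0.80; 66 per arm; equal arms. With equal arms, the two contrasts at one visit share the CogniFit arm, so their correlation is 0.5.

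**Assumption:** the correlation between the 3-month and 6-month contrasts is not given. It is varied from 0 to 0.9. As in the protocol's formula, d is applied to follow-up scores with known variance.

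**1. The plan's own figure.**
- Per-test level: 1 − 0.95^(1/4) = 0.01274; half is 0.0064; z = 2.491.
- n per arm = 2(0.842 + 2.491)² / 0.58² = 66.03, or 65.99 with z = 2.49. This matches 66.
- Power of one contrast at n = 66: 80.0%.

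The stated figures reproduce. The exponent printed as 4 is most likely a 1/4 lost in typesetting, since 0.01274 is the correct value, so it is not counted as an error.

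**2. Both controls at one named visit, single level.** Each statistic has mean 0.58 / √(2/66) = 3.332. The probability that two normal statistics with correlation 0.5 both exceed 2.491 is 0.687, or about 69%. It does not depend on the between-visit correlation.

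**3. Other definitions of success, single level, d = 0.58 on all four tests (simulation).**

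| Success means | Between-visit correlation | Power |
|---|---|---|
| One given contrast | any | 80% |
| Both controls at one named visit | any | 69% |
| Both controls at either visit | 0.5 to 0.7 | 84% to 80% |
| All four tests | 0.5 to 0.7 | 54% to 57% |
| At least one of four | 0 to 0.9 | 99% to 94% |

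The last row is the same under Holm-Sidak, because the first threshold is the same.

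**4. Holm-Sidak.** The ordered p-values are compared with 1 − 0.95^(1/k) for k = 4, 3, 2, 1: 0.0127, 0.0170, 0.0253 and 0.05, stopping at the first failure. Power for both controls at one named visit:

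| Effect at the other visit | Single level | Holm-Sidak |
|---|---|---|
| d = 0.58 | 69% | 83%, 82%, 81%, 81% (correlation 0, 0.5, 0.7, 0.9) |
| d = 0.40 (correlation 0.5) | 69% | about 76% |
| None | 69% | about 73% |

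Simulated family-wise error under the global null is 3.6% to 4.8% for either rule, falling as the between-visit correlation rises.

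**5. The analysis text as written, 0.05 per test.** Family-wise error over the four primary tests is about 16% at between-visit correlation 0.5 and about 15% at 0.7. If the four tests were independent it would be 1 − 0.95⁴ = 18.5%. Power for both controls at one visit would be 85.6%, but without control of the overall 5%.

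**The case against.** **Nothing in the sample size section is misstated.** It prints the formula and the per-test alpha, and it never calls 0.8 a joint power. Sizing on one adjusted contrast is a common convention, and the single Sidak level is valid. This stands, so the change is an improvement and not the correction of an error.

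**A reader might infer that 69% is the power of the trial's stated purpose.** The documents do not support this. Trial design names two comparators but does not say that both must be beaten at one named visit, and it adds that the gaming types are to be assessed separately. The primary hypothesis uses *or* and *and/or*; on that wording, power is about 94% to 99% under either rule. What stands is that the two sections point to different criteria and the protocol does not choose between them.

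**A reader might infer that the four tests are in fact protected by Sidak.** They are not, on the text shown: the level appears only in the sizing, and the analysis section says P < 0.05. An edit confined to the sample size paragraph and the modelling paragraph would therefore not take effect.

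**The step-down gain of about 13 points is a best case.** It needs d = 0.58 at both visits. That is the protocol's own planning value, but *and/or* allows an effect at one visit only, and then the gain is about 4 points. A smaller effect against the active control also matters: with d = 0.40 there and 0.58 against usual care (between-visit correlation 0.5), the figures are 39% and 54%. The gain shrinks but does not reverse.

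**A statistical analysis plan might choose the step-down.** It might, but the protocol itself states both a single level and a conflicting blanket P < 0.05, and these need reconciling in any case.

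**Conclusion.** The point holds in a limited form. The 80% is the power of one contrast at the single Sidak level and is correctly calculated. Beating both controls at one named visit has a power of about 69%, given 66 per arm and d = 0.58 against each control. Whether that is the relevant figure depends on a success criterion that the hypotheses and the Trial design section leave open. It should not be read as a finding that the trial is underpowered for its primary hypothesis.

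The firmer defect is that the adjusted level is absent from the analysis text. At P < 0.05 in all tests, the family-wise error over the four primary contrasts is about 15% to 16% for between-visit correlations of 0.7 to 0.5.

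Holm-Sidak keeps the overall 5% and is never less powerful than the single level. For both controls at one visit it gives about 73% to 83%, depending on the effect at the other visit. These figures use the protocol's simple two-group formula; the planned group-by-time interactions also depend on within-patient correlations that the protocol does not give.

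**What to change.** 1. In the closing paragraph on significance under Cognitive and clinical outcomes, exempt the four primary contrasts from the blanket P < 0.05. Test them by Holm-Sidak: ordered p-values against 0.0127, 0.0170, 0.0253 and 0.05, stopping at the first failure. Make the modelling paragraph and the sample size section consistent with this.
2. In the sample size section, state that 80% is the power of one contrast under the single-step level.
3. Reconcile The hypotheses with Trial design on which result counts as success, and report the power for that result with its assumptions. If success means both controls at one visit: 69% single-step; step-down 81% to 83% with d = 0.58 on all four tests, about 76% with d = 0.40 at the other visit, and about 73% with no effect there.

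The cost is a few sentences of text, with no extra patients, visits or data. The downside is that simultaneous confidence intervals matching a step-down rule are less simple. The single-step 98.7% intervals (1 − 0.01274) can be reported beside the step-down decisions.

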**Methods:**

The participants will be recruited from different outpatient units (e.g., outpatient psychiatric units, day hospitals, residential care homes). The controlled clinical trial will follow a three-arm parallel-group design: 1) cognitive training (experimental group, CogniFit), 2) entertainment gaming (active control group, SIMS 4), and 3) treatment as usual. The primary outcomes are working memory function at 3-month and 6-month follow-ups. The secondary outcomes are patients’ other cognitive and social functioning, the ability to experience pleasure, self-efficacy, and negative symptoms at 3-month and 6-month follow-ups. We will also test the effectiveness of gaming interventions on neurocognitive outcomes (EEG and 3 T MRI plus rs-fMRI) at a 3-month follow-up as an additional secondary outcome. Data will be collected in outpatient psychiatric services in Hong Kong. Participants will have a formal diagnosis of schizophrenia and be between 18 and 60 years old. We aim to have a total of 234 participants, randomly allocated to the three arms. A sub-sample of patients (*N* = 150) will be recruited to undergo an EEG. For neuroimaging assessment, patients will be randomly allocated to a subset of patients (*N*=126). We will estimate the efficacy of the interventions on the primary and secondary outcomes based on the intention-to-treat principle. Behavioural and EEG data will be analysed separately.

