### Interventions

Participants will be allocated into three groups: 1) cognitive training with computerised exercises (G1, CogniFit, *N*=78), 2) entertainment video gaming (G2, Entertainment Gaming, *N*=78), and 3) treatment as usual (*N*=78). CogniFit and entertainment games (SIMS 4) represent two distinct gaming genres: CogniFit is a cognitive training package with computerised exercises aiming to improve cognitive abilities based on a personalised brain training regimen. SIMS 4 is a pure entertainment game without any known health impact. The administration of both interventions will include 60 pre-scheduled gaming sessions [38] at the study settings as part of the normal day programme, lasting from 45 to 60 min each, at least 5 days/week [17], 60 h in total. The gaming schedule can also be tailored based on the participants’ needs (working, studying, family issues) as long as the gaming hours are in line with the total hours planned. Individual gaming sessions on separate computers will be conducted in small groups (about 3–6 per group) and closely monitored by the trained research assistant. Monitoring of gaming sessions is crucial to ensure intervention fidelity. This was exemplified in our feasibility study, which showed that, out of all possible 60 pre-scheduled sessions, 97% of sessions were realised as planned, and all participants enjoyed gaming. Gaming hours (diaries, automatic gaming logs) for each gaming session will be recorded to provide evidence of the intervention fidelity; a minimum of 50 gaming hours will be acquired to ensure observable neuroplasticity after gaming [19]. To report any negative side effects of gaming (e.g., tiredness of eyes), feedback and any concerns will be reported in a gaming diary after each gaming session [39].

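### The number to be randomised is given as both 237 and 234, and the 16% dropout is worded for the intervention period although 198 participants are promised at both follow-ups

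*Protocol article*

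**What the plan says.** All references are to the protocol article.

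- **Power analysis and sample size, requirement.** The calculation uses an effect size of 0.58, a power of 0.8 and a two-sided per-test level of 0.01274, adjusted for four tests. It arrives at 66 per group, 198 in all. On the tests it says: "Four pairwise interactions between the contrast of the two comparisons and the two time points will be tested". The primary endpoints are verbal working memory at 3 and at 6 months, so two of the four tests fall at 6 months.
- **Power analysis and sample size, inflation.** The only dropout rate for the main sample is that "around 16% will drop out during the course of intervention". From it the plan derives "237 participants to be randomly allocated to three study groups (79 patients/group) to ensure a final sample of 198 participants in the follow-ups".
- **Abstract, Methods.** "We aim to have a total of 234 participants, randomly allocated to the three arms".
- **Interventions.** Each of the three arms is listed with N = 78, which sums to 234.
- **Timing.** The Recruitment section gives the intervention as 12 weeks. Data collection and follow-up places the 3-month assessment after the intervention and the last one 6 months after baseline.

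**The concern.** Two different totals stand in the current text as the number to be randomised, and they cannot both come from one calculation. A reader checking whether the trial reached its target has two answers.

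The second issue is the period that the dropout rate covers. A rate worded for the 12-week intervention takes the trial to month 3. The plan then promises the same 198 participants at the follow-ups, in the plural. Read literally, this assumes that nobody is lost between months 3 and 6. At stake is whether the stated 80% power describes the 6-month tests as well as the 3-month tests.

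**Working it through.** **Inputs (Power analysis and sample size).** Effect size 0.58; family-wise alpha 0.05 two-sided; four tests; power 0.80; equal groups; dropout 16%.

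**Step 1: reproduce the plan's requirement.**
- Per-test alpha = 1 − 0.95^(1/4) = 0.01274, or 0.0064 per tail, z = 2.491 (the plan prints 2.49).
- n per group = 2(2.49 + 0.8416)²/0.58² = 65.99, so 66. With unrounded z it is 66.03.
- Power = Φ(0.58·√(n/2) − 2.491). At n = 66: Φ(3.332 − 2.491) = 80.0%.

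The plan's 66 per group and 198 in total reproduce.

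**Step 2: inflate for dropout.**
- Per group: 66/0.84 = 78.57, so 79, and 3 × 79 = 237.
- On the total: 198/0.84 = 235.7, so 236.
- The stated 1,073 to be approached, with 60% ineligible and 45% refusing, gives 1,073 × 0.40 × 0.55 = 236.1.

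All of this agrees with 236–237. None of it produces 234.

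**Step 3: compare the two totals under 16% dropout.**

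| Randomised | Expected to remain | Per group | Power |
|---|---|---|---|
| 237 (79/group) | 237 × 0.84 = 199.1 | 66.4 | 80.2% |
| 234 (78/group) | 234 × 0.84 = 196.6 | 65.5 | 79.6% |

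The shortfall with 234 is 198 − 196.6 = 1.4 participants overall, and about 0.4 percentage points of power.

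**Step 4: what the 6-month tests would have if the 16% stops at month 3.** The article gives no loss rate for months 3 to 6. The further losses below are assumptions for illustration, applied to those remaining at month 3.

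| Further loss (assumed) | From 79/group: n, power | From 78/group: n, power |
|---|---|---|
| 0% | 66.4, 80.2% | 65.5, 79.6% |
| 5% | 63.0, 77.8% | 62.2, 77.2% |
| 10% | 59.7, 75.1% | 59.0, 74.5% |

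From 79 per group, the effect detectable with 80% power is 0.58 × √(66.03/63.0) = 0.59 at 5% further loss and 0.58 × √(66.03/59.7) = 0.61 at 10%.

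**Step 5: check against the block size.** Randomisation is in blocks of 6 at 1:1:1. 234/6 = 39 complete blocks, exactly 78 per arm. 237/6 = 39.5, so recruitment would end mid-block. The three patients beyond block 39 could add 0 to 2 to any one arm, so 79 per arm is not guaranteed.

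**The case against.** Several arguments limit this point, and most of them stand.

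- **The difference between 234 and 237 is immaterial for power.** A reader might infer that 234 leaves the trial underpowered. It does not: 0.4 percentage points is negligible beside inputs that the plan itself gives as approximate. What remains is an inconsistency in a stated design figure.
- **The 16% may be meant as total loss.** The plan applies it to reach 198 at the follow-ups, so the authors may intend it to run to month 6, and power then stays near 80%. This is a fair reading, but the wording ties the rate to the intervention, and the source of the rate cannot be checked from the article.
- **The 6-month figures are not the power of the planned analysis.** They come from the plan's two-sample formula applied to completers. The Data analysis section plans an intention-to-treat multilevel model over all time points, in which a patient seen at baseline and 3 months still contributes. The primary hypothesis is also framed as benefit at 3 and/or 6 months, so the power of the 6-month tests alone is not the power for that hypothesis. Both points stand.
- **The recruitment rule does not show that enrolment will stop short.** A reader might infer that recruitment may close at 234 and miss the requirement. The Recruitment section ties closure to the planned numbers being reached for analysis. That can be read as the analysed 198 as easily as a randomised total, so the inference is not supported.

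**Conclusion.** Two things hold. First, the randomised total is inconsistent: 237 in the sample size section, 234 in the Abstract and Interventions section. Only 237 follows from the plan's stated requirement and dropout rate. The cost of 234 is about half a patient per group and 0.4 points of power. Second, as worded, the dropout allowance ends with the intervention while the 198 is claimed at both follow-ups, so loss between months 3 and 6 is not visibly provided for.

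It would be tempting to conclude that the 6-month tests lack 80% power. The document does not establish this. The conclusion would need the 16% to exclude months 3 to 6, a further loss that the article does not state, and a completers-only analysis that is not the one planned. The 75–78% for 79 per group illustrates a further 5–10% loss and is not a finding about this trial. The point is minor.

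**What to change.** 1. Use one randomised total in the Abstract, the sample size section and the Interventions section. There are two consistent choices:
   - 237 (79 per group), which follows from the plan's own calculation, with a note that it ends mid-block with blocks of 6, so the arms may not be exactly equal; or
   - 234 (78 per group, 39 complete blocks), with the expected completers restated as about 65.5 per group and power as about 79.6%.
2. Add a sentence saying whether the 16% is total loss to month 6. If so, the 198 and the 80% can stand for both follow-ups with 237.
3. If the 16% covers only the intervention, limit the 80% claim to 3 months. Restate 6-month power, or the detectable effect, under an explicit assumed further loss, noting that the formula counts completers and that the multilevel model may recover some information.

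The cost is wording in three places and one added sentence. Choosing 237 means three more patients than 234, already included in the plan's own calculation. If step 3 applies, the plan also states a somewhat lower 6-month power.
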